***Secondary objectives***

To determine if chloroquine shortens the duration of hospital stay.To determine if chloroquine results in more ventilator-free days.To determine if chloroquine use results in better survival compared with standard of care.To define the safety profile of chloroquine in COVID-19.

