### Study design

The study will start with a 10-patient prospective observational pilot study following the same entry and exclusion criteria as for the randomized trial and undergoing the same procedures. All 10 participants will receive chloroquine at the doses used in the trial; they will not be randomized. The purpose of the pilot study is to develop the study procedures for the randomized controlled trial, including the safe monitoring of participants, and to acquire some preliminary data on the safety of chloroquine in those with COVID-19 in Vietnam. Data from these patients will not be included in the final analysis. Once the pilot study has been completed, and the data reviewed by the trial steering committee (TSC), the data monitoring committee (DMC), and the Ministry of Health (MoH) ethics committee (EC), we will proceed with the trial. We aim for minimum delay between completing the pilot study and starting the randomized trial.

The main study is an open label, randomised, controlled trial with two parallel arms of standard of care (control arm) versus standard of care with 10 days of chloroquine (intervention arm) with a loading dose over the first 24 hours, followed by 300mg base orally once daily for nine days. The study will recruit patients in three sites in Ho Chi Minh City, Vietnam: the Hospital for Tropical Diseases (HTD), the Cu Chi Field Hospital, and the Can Gio COVID hospital. Additional sites including the National Hospital for Tropical Diseases in Ha Noi, Vietnam will be added based on enrolment rates.

All adult patients (≥18 years old) presenting to the study centres with positive throat/nose swabs (RT-PCR) for SARS-CoV-2 and requiring hospital admission will be eligible for study inclusion subject to the inclusion and exclusion criteria. Randomization will be stratified by severity of illness with severe disease being defined by a SpO2 ≤94%, or tachypnea (respiratory rate ≥24 breaths/min), and mild-moderate disease being defined by SpO2 >94% and respiratory rate <24 breaths/min without supplemental oxygen.

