***Secondary endpoints***

The duration of hospital stay from the time of randomization.The number of ventilator-free days during the first 28 days following randomization.The time to (all-cause) death following the first 10, 28, and 56 days since randomization.The WHO ordinal outcome scale for COVID-19 at days 28, 42 and 56
^24^.Fever clearance time (defined as temperature <37.5°C for 48 hours).Development of acute respiratory distress syndrome (ARDS) defined by the Kigali criteria
^25^.Oxygenation-free days over the first 28 days.Risk of serious adverse events (SAEs).Risk of grade 3 or 4 adverse events (AEs).

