***Randomization and treatment allocation***. Randomization will be 1:1 to either chloroquine or standard of care treatment. Randomization with variable block sizes of four and six will be used to assign subjects to treatment. Randomization will be stratified by recruiting centre and disease severity. The randomization list will be generated according to the OUCRU randomization and drug dispensing SOP. In brief, the study statistician will set up statistical code to generate the randomization list and transfer it to the central study pharmacist. The study pharmacist will change the random seed, i.e. the initialization of the random numbers generator, in the statistical code in order to blind the study statistician and then run the code to prepare the final randomization list for treatment preparation. The randomization list will be password protected and stored on a secure server to which only the study pharmacist has access. Based on the randomization list, the study pharmacist will prepare randomization envelopes and generate identical sealed treatment packs for each study ID and distribute them to the sites in batches as required. Each pack will contain sufficient chloroquine for the 10 days of treatment. Enrolment logs specific to each study site will be used to assign participants to the next available sequential number and corresponding sealed treatment pack.

***Study intervention***. Chloroquine will be administered orally, as tablets. For unconscious participants chloroquine can be crushed and administered as a suspension via a nasogastric tube. A loading dose, administered with food where possible, is given on the first study day. Following the first 24 hours, participants will receive a dose of chloroquine phosphate salt of 500mg once daily until 10 days after randomization (unless they are <53kg, when the dose will be reduced, see
Table 2).

Chloroquine has complex pharmacokinetic properties with an enormous apparent volume of distribution (200–300 L/kg) and a terminal elimination half-life of 1–2 months, so concentrations in plasma (and rapidly exchanging tissue compartments) are determined predominantly by distribution not elimination. Given that EC50 values against the SARS-CoV-2 virus are in the low micromolar range
*in vitro*, which suggests moderate activity, it is likely that relatively high concentrations will be required for maximum effects

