Biological specimens and laboratory evaluations: On study entry all participants will have a review of clinical investigations done so far. Where an investigation has been performed within the last 24 hours, the results will be recorded, and they will only be repeated if clinically indicated. Study entry laboratory tests will be performed as per the study schedule below.

***Subsequent assessments***. Participants will have daily assessment as per standard of care while in-patient by the hospital staff. While in-patient the study will collect the following data: peripheral oxygen saturation (pulse oximeter), respiratory rate, and FiO2. The use of a ventilator or other non-invasive ventilation device will be recorded each day. Participants will have clinical assessment recorded as per the trial assessment schedule (see
Table 3). The decision to discharge patients will be at the discretion of the attending physician and will depend upon the clinical status of the patient. According to current standard of care, recovery and hospital discharge is dependent upon the patient having had at least two daily consecutive negative PCR throat/nose swabs. Following discharge, participants will be seen on days 28, 42 and 56 post-randomization.

**Table 3. T3:** Trial assessment schedule.

Procedures	Screening	Enrollment/Baseline (Visit 1)	Follow-Up (Visit 2)	Follow-Up (Visit 3)	Follow-Up (Visit 4)	Follow-Up (Visit 5)	Follow-Up (Visit 6)	Follow-Up (Visit 7)	Daily visits to discharge	Day 28 visit	Day 42 visit	Final Study Visit (Day 56)
Informed consent	x											
Demographics	x											
Medical history	x											
Randomization	x											
Physical exam	x	x	x	x	x	x	x	x	x	x	x	x
Throat/nose swab for viral PCR		x	x	x	x	x	x	x	x			
Vital signs	x	x	x	x	x	x	x	x	x			
Weight		x										
CBC w/diff, plts		x		x		x		x				
Serum chemistry ^a^	x			x		x		x				
Blood store (3-5 mls)		x						x				x
ECG (as indicated) ^b*^		x										
CXR	x								x (discharge)			x
Adverse event evaluation			x	x	x	x	x	x	x	x	x	x
WHO ordinal outcome scale **									x (discharge)	x	x	x
EQ5D questionnaire **										x		x
Estimated total blood volumes ml per day ms	6–10	10–12		10–12		10–12		10–12				3–5
Total blood volume over course of study mls (both clinical and research purposes)												52–63

^a^ Urea, Creatinine, ALT, bilirubin

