Probable	There is evidence to suggest a causal relationship and the influence of other factors is unlikely.	SAR
Definitely	There is clear evidence to suggest a causal relationship and other possible contributing factors can be ruled out.	SAR

SAE, serious adverse event; SAR, serious adverse reaction.

Expectedness

If an AE or AR is not expected with COVID-19 disease or with chloroquine, then it is unexpected. An unexpected adverse reaction (UAR) is one not previously reported in the current Summary of Product Characteristics (SPC) at the time the event occurred, or one that is more frequent or more severe than previously reported. The definition of an UAR is given in
Table 4. If an SAR is assessed as being unexpected, it becomes a suspected unexpected serious adverse reaction (SUSAR).

Investigators should always check the current version of the SPC. Expected toxicities associated with chloroquine are:
Frequency unknown: Abdominal pain; agranulocytosis; alopecia; anxiety; atrioventricular block; bone marrow disorders; confusion; corneal deposits; depression; diarrhoea; eye disorders; gastrointestinal disorder; headache; hearing impairment; hypoglycaemia; hypotension; insomnia; interstitial lung disease; movement disorders; myopathy; nausea; neuromyopathy; neutropenia; personality change; photosensitivity reaction; psychotic disorder; QT interval prolongation; seizure; severe cutaneous adverse reactions (SCARs); skin reactions; thrombocytopenia; tinnitus; tongue protrusion; vision disorders; vomiting.Rare or very rare: Cardiomyopathy; hallucination; hepatitisOverdose: Overdose is difficult to treat and can result in life-threatening features including arrhythmias (which can have a very rapid onset) and convulsions (which can be intractable). Hypoglycaemia can also feature. However, treatment in this study will be directly observed as an in-patient and therefore is extremely unlikely.

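### If chloroquine patients who meet the discharge condition early stay in hospital to finish the observed 10-day course, actual length of stay is biased against chloroquine; the protocol article does not say what happens to them

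*Protocol article*

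**What the plan says.** **Endpoint.** The first secondary objective in the protocol article is "To determine if chloroquine shortens the duration of hospital stay". The matching endpoint, also listed first, is "The duration of hospital stay from the time of randomization".

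**Treatment.** Study procedures (Study intervention) gives chloroquine phosphate "500mg once daily until 10 days after randomization" after the first 24 hours, with a lower dose below 53 kg. Table 2 shows two doses on the first day, then once-daily dosing for 9 days. Safety reporting (Expectedness, overdose entry) says that "treatment in this study will be directly observed as an in-patient". Controls receive standard of care and no study drug.

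**Discharge.** Study procedures (Subsequent assessments) gives one rule for both arms. It says "The decision to discharge patients will be at the discretion of the attending physician", that clinical status counts, and that under current standard of care "recovery and hospital discharge is dependent upon the patient having had at least two daily consecutive negative PCR throat/nose swabs".

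**Blinding.** "The main study is an open label, randomised, controlled trial with two parallel arms" (Study design), so the discharging physician knows who still has doses due.

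**The concern.** The treatment and discharge statements meet in any chloroquine patient who satisfies the discharge condition before the course is over. There are three ways out:

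- The patient stays to complete the observed course, for a reason that no control has.
- The patient goes home with doses still to take, against the statement on in-patient observation.
- The patient stops early, against the stated course length.

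The article does not choose between them, and sites or physicians could differ. To the extent that the first is followed, actual length of stay partly measures course length in one arm only. A real shortening would be understated, and a drug with no effect could appear to prolong stay. Analysis of the discharge date alone cannot repair this, because the distortion arises in trial conduct.

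**Working it through.** **Inputs from the Statistics section.** Log-normal clearance time T with mean 2.17 and SD 0.74 on the natural-log scale; factor 0.76 at N = 240 and 0.68 at N = 120; 1:1 allocation. The control median is exp(2.17) = 8.76 days.

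**Reproducing the plan's power** (two-sided alpha 0.05 assumed; none is stated). SE = 0.74 × √(4/N).
- N = 240: SE = 0.0955; power = Φ(0.2744/0.0955 − 1.96) = 81.9%.
- N = 120: SE = 0.1351; power = Φ(0.3857/0.1351 − 1.96) = 81.4%.

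Both agree with the stated 80%, so the planning model is read as intended.

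**Assumptions added here.** Earliest discharge is T + L. The central value is L = 1.5 days: about 0.5 day from the midpoint to the first negative swab, then 1 day to the second. The range shown is 0 to 3. A hold means chloroquine stay = max(floor, T + L). The floor is day 10 (dosing until 10 days after randomisation) or day 9 (Table 2 read as day 0 plus nine daily doses). Means are truncated at day 28.

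**Share ready before day 10** = Φ[(ln(10 − L) − 2.17 − ln f)/0.74]. At L = 1.5:
- Control, f = 1: Φ[(2.140 − 2.170)/0.74] = 48%.
- Chloroquine, f = 0.76: Φ[(2.140 − 1.896)/0.74] = 63%.

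**Difference in truncated mean stay, chloroquine minus control, f = 0.76, every early-ready patient held.** The mean is the area under the curve of P(stay > t) from 0 to 28, with that probability set to 1 before the floor.

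| L (days) | Chloroquine ready before day 10 | No hold | Day-9 floor | Day-10 floor |
|---|---|---|---|---|
| 0 | 71% | −2.3 | +0.4 | +1.0 |
| 1.5 | 63% | −2.3 | −0.5 | +0.1 |
| 2 | 60% | −2.3 | −0.8 | −0.2 |
| 3 | 53% | −2.2 | −1.2 | −0.7 |

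At L = 1.5 the means behind the row are 12.2 days for control, against 9.9 (no hold), 11.7 (day 9) and 12.3 (day 10) for chloroquine. The medians are 10.3 for control, against 8.2, 9.0 and 10.0. Without truncation, the saving of 2.75 days falls to 0.4 day with the day-10 floor.

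**No drug effect** (f = 1, L = 1.5, day-10 floor): 13.8 v 12.2 days, so the hold alone adds 1.6 days.

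**Power for stay** (500 simulated trials, 120 per arm, L = 1.5, day-10 floor, all stays observed). At f = 0.76, log-rank finds a shorter stay on chloroquine in about 75% of trials with no hold, 24% if half of the early-ready patients are held, and 2% if all are. With no drug effect and all held, about 43% of trials show a significantly longer stay on chloroquine.

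**The case against.** The strongest reply is that no retention rule exists. The in-patient sentence is a remark on why overdose is very unlikely, placed in a list of expected toxicities. The only discharge rule is the same in both arms. The Table 3 footnote on ECG monitoring allows for discharge before day 14, and the per-protocol set excludes only those with less than one week of chloroquine. Both are compatible with stays or courses shorter than planned. The full protocol or the dispensing SOP may also cover doses outstanding at discharge. This stands: a reader might infer a fixed minimum stay of 9 to 10 days on chloroquine, but the documents do not state one. Full retention is an upper bound.

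A reader might also infer that any benefit on stay must vanish. The table does not support that: the result depends on lag and floor, and a saving survives in several rows.

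A third inference is that stay merely restates viral clearance. Two negatives are necessary but not sufficient, since discretion and clinical status also count. T + L is therefore close to the earliest discharge, and the overlap with the primary endpoint is substantial but not complete.

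Finally, the analysis of this endpoint is left to the SAP, and PCR-based discharge is described as current standard of care, so actual stay does measure real bed use. Both are true. Neither says what happens to the early-ready chloroquine patient.

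**Conclusion.** The point holds in conditional form. The statements on course length, in-patient observation and discharge leave a gap that, on the planning model, concerns about 63% (53 to 71%) of the chloroquine arm at factor 0.76. If all of these patients are kept in, the mean saving of about 2.3 days falls to about zero with a day-10 floor at lag 1.5 (from 1.0 day longer at lag 0 to 0.7 day shorter at lag 3), or to 0.5 day with a day-9 floor at lag 1.5. With no drug effect, retention adds about 1.6 days (day-10 floor, lag 1.5). Partial retention does proportionately less but still costs much of the power.

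These figures rest on a planning distribution estimated from 14 patients, on the assumed lag, and on discharge as soon as the swab condition is met. The clock and the written discharge rule are the same in both arms; the possible asymmetry lies in what determines actual discharge. This is a secondary endpoint, and the mechanism does not touch the time to viral clearance.

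**What to change.** 1. Reconcile Study intervention, Subsequent assessments and the overdose entry in Safety reporting on what happens when a chloroquine patient meets the discharge condition before the course ends. The sponsor decides the rule; none is proposed here.
2. Analyse time from randomisation to first meeting the trial's own discharge condition: two consecutive daily negative swabs plus prespecified clinical-status criteria taken from data already collected daily in hospital (SpO2, respiratory rate, FiO2, ventilation). Apply it identically in both arms, whether or not doses remain.
3. Report actual length of stay beside it.
4. State that, because PCR negativity is part of the condition, this endpoint overlaps the primary and is not independent evidence of clinical benefit.

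Removing the PCR part to avoid the overlap would not work. The mild-moderate stratum is defined by SpO2 above 94% and respiratory rate below 24 without oxygen, so many of those patients could meet purely clinical criteria at randomisation.

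The cost is protocol and SAP wording and one derived variable, with no extra patients or visits. The small downside is an endpoint less familiar than the discharge date.

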*in vivo*. The intervention dose was chosen following evidence review and discussion with healthcare partners. We aimed for an initial loading dose of 10mg/kg base, followed by 5mg/kg base at 6 hours and every 24 hours until 10 days after randomization. The (maximum) dosage used for an adult ≥53 kg is as shown in
Table 2.

**Table 2. T2:** A) Maximum chloroquine dose for an adult ≥53 kg enrolled in the VICO trial. B) Maximum chloroquine dose for an adult <53 kg enrolled in the VICO trial.

**A**			
		Total chloroquine (CQ) dose	
Time	Number of tablets	Chloroquine base	Chloroquine phosphate
Initial dose T=0	4	600mg	1000mg
T=6 hours	2	300mg	500mg
Thereafter	2 once daily for 9 days	300mg once daily	500mg once daily
**B**			
	For an adult 52-45 kg	For an adult <45-38 kg	For an adult <38 kg
Time	Number of tablets	Number of tablets	Number of tablets
Initial dose T=0	3.5	3	2.5
T=6 hours	2	1.5	1.5
Thereafter	2 once daily for 9 days	1.5 once daily for 9 days	1.5 once daily for 9 days

Patients with severe renal impairment or elevated blood transaminases are excluded from the study (see inclusion and exclusion criteria). If an enrolled patient develops cardiac arrhythmia or syncope, chloroquine will be stopped and an electrocardiogram (ECG) performed. Electrolytes (Na, K, Ca, Mg) will be checked and corrected as necessary. Where significant asymptomatic QTc prolongation is identified (>500ms), chloroquine administration will be interrupted, electrolytes checked and corrected, and the drug reintroduced when the QTc is <480ms. Particular care will be taken in those who take other medications, which may prolong QTc.

***Baseline assessment***.

Clinical assessment: All participants will have a full clinical assessment including medical history and examination by the study team. Data collected will include presenting symptoms, duration of illness, past medical history, current medications, and physical examination findings including vital signs (pulse, temperature, blood pressure, oxygen saturations and FiO2), and the results of cardiovascular, respiratory, gastrointestinal and neurological examination in line with standard clinical practice.

Radiology: The results of any radiological imaging (chest X-ray, computed tomography (CT) scan, lung ultrasound) performed during the participant’s illness will be recorded in the clinical reporting form. Participants who have not had a chest X-ray will undergo a chest X-ray on study entry.

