^b^ Daily ECGs performed if on other medication which can prolong QTc. Additional investigations performed for clinical care can be recorded in the study CRF in order to help understanding of the clinical course. * In HTD and if the patient is in ICU, ECG will be measured continuously every one hour daily for 14 days or until discharge if earlier. ** May be administered by telephone call. Note: if it is impossible for the patient to attend day 28, 42, and 56 visits (e.g. community in lockdown, or hospital closed to non-COVID patients) then follow-up can occur entirely by phone. PCR, polymerase chain reaction; CBC, complete blood count; ECG, electrocardiogram; CXR, chest X-ray; WHO, World Health Organization; ALT, alanine aminotransferase; CRF, case report form; HTD, Hospital for Tropical Diseases; ICU, Intensive Care Unit.

In a subset of participants admitted to HTD we will monitor ECG changes, using real-time monitoring. Participants will have up to one-hour ECG continuous recordings daily. The ECG recording will be downloaded from a standard monitor (GE Careview) and stored electronically. ECG changes (including QT interval) will then be analysed by machine learning.

***Discontinuation of treatment and participation***. Each participant has the right to withdraw from the trial at any time. In addition, the investigator may discontinue a participant from the trial at any time if the investigator considers it necessary for any reason including:
Ineligibility (either arising during the trial or retrospectively having been overlooked at screening)Significant protocol deviationSignificant non-compliance with treatment regimen or trial requirementsAn AE which requires discontinuation of the trial medication or results in inability to continue to comply with trial proceduresDisease progression which requires discontinuation of the trial medication or results in inability to continue to comply with trial procedures
Withdrawal of consentLoss to follow up

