### Safety reporting

The safety profile of chloroquine is well understood and the risks related to chloroquine phosphate/sulphate/hydrochloride are very low, unless the drug is taken in overdose
^28^. Most side effects are infrequent. Adverse reactions (ARs) relating to the cardiovascular system, the central nervous system, the skin, hypoglycaemia, hypersensitivity, gastrointestinal, and retinal toxicity have all been described, though usually after high doses and protracted exposures. The main adverse effect is itching in dark-skinned individuals; Africans are much more commonly affected compared to Asians. Adverse effects will be classified and graded according to the Common Terminology Criteria for Adverse Events (CTCAE) system
^29^. All serious and grade 3 or 4 AEs will be compared between arms and reported by frequency per arm. An independent DMC will oversee the safety of the trial participants.

***Definitions***. The definitions of the principles of International Conference on Harmonization (ICH) Good Clinical Practice (GCP) apply to this trial protocol (see
Table 4).

**Table 4. T4:** International Conference on Harmonization (ICH) Good Clinical Practice (GCP) definitions.

Table	Definition
Adverse event (AE)	Any untoward medical occurrence in a participant or clinical trial subject to whom an investigational medicinal product has been administered including occurrences that are not necessarily caused by or related to that product.
Adverse reaction (AR)	Any untoward and unintended response to an investigational medicinal product related to any dose administered.
Unexpected adverse reaction (UAR)	An AR, the nature or severity of which is not consistent with the information about the investigational medicinal product in question set out in the Summary of Product Characteristics (SPC) for that product.
Serious adverse event (SAE) or serious adverse reaction (SAR) or suspected unexpected serious adverse reaction (SUSAR)	Respectively any AE, AR or UAR that: Results in death Is life-threatening * Requires hospitalisation or prolongation of existing hospitalisation ** Results in persistent or significant disability or incapacity Consists of a congenital anomaly or birth defect Is another important medical condition ***

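### No glucose is scheduled in either arm although hypoglycaemia is listed as an expected chloroquine reaction, so mild or silent cases depend on unscheduled tests ordered by staff who know the arm

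*Protocol article*

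**What the plan says.** **Scheduled chemistry.** Table 3 (Study procedures) marks serum chemistry at screening and at Visits 3, 5 and 7. Footnote a gives its content as a closed list: "Urea, Creatinine, ALT, bilirubin". No glucose, sodium, potassium, calcium or magnesium is in it, and the article mentions glucose measurement nowhere else.

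**Expected reactions.** The opening of Safety reporting includes hypoglycaemia among the reactions described for chloroquine ("the skin, hypoglycaemia, hypersensitivity"). The Expectedness subsection lists it again ("hearing impairment; hypoglycaemia; hypotension; insomnia"), together with QT prolongation, and mentions it once more as a feature of overdose.

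**Use of safety data.** Characterising the drug's safety is a secondary objective. Serious and grade 3 or 4 adverse events are secondary endpoints, are compared by arm, and go to the data monitoring committee by arm.

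**Who knows the allocation.** Study design states: "The main study is an open label, randomised, controlled trial with two parallel arms". Only the technicians running the PCR are said to be unaware of treatment.

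**Electrolytes and ECG.** Study intervention provides for electrolytes after arrhythmia, syncope or a QTc above 500 ms: "Electrolytes (Na, K, Ca, Mg) will be checked and corrected as necessary". ECG is handled separately. Table 3 marks it once, at baseline and as indicated, and the footnotes add "Daily ECGs performed if on other medication which can prolong QTc" as well as recordings at the Hospital for Tropical Diseases and in intensive care.

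**The concern.** A between-arm comparison of an adverse reaction is fair only if both arms have the same chance of having it found. For hypoglycaemia without clear symptoms, that chance depends on a glucose measurement, and the plan schedules none. Whether one is made is left to treating staff who know who is taking chloroquine and who hold a toxicity list naming hypoglycaemia. The protocol also provides for unconscious and comatose participants (Study intervention; Risks and benefits), who cannot report symptoms.

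At stake is one component of the safety comparison. If chloroquine patients are tested more often, the drug may appear to cause hypoglycaemia when it does not. If few patients are tested in either arm, real cases are missed. The primary virological endpoint is not affected.

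**Working it through.** The plan gives no figure for hypoglycaemia, so there is nothing to reproduce. The check traces how a case would reach the analysis, and then illustrates the arithmetic.

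**Step 1: scheduled opportunities to measure glucose.** Chemistry is drawn four times: at screening and at Visits 3, 5 and 7. Screening precedes treatment, so 4 − 1 = 3 draws could show a drug effect. None of the four includes glucose or an electrolyte. The article does not give day numbers for Visits 2 to 7; I assume that the three later draws fall during or soon after the 10 treatment days.

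**Step 2: remaining routes of detection.**
- Clinical route: daily in-patient assessment, and adverse event evaluation at every visit after baseline. It runs in both arms and can bring symptomatic events to light.
- Laboratory route: tests ordered for clinical care. The Table 3 footnotes permit, but do not require, these to be entered in the case report form.

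**Step 3: from a result to an adverse event.** Under Assessment of AEs, an abnormal laboratory value must be recorded as an event only if an intervention followed; otherwise the investigator decides. Stopping, reducing or delaying a current treatment counts as an intervention, and only one arm has study drug to stop. Non-serious grade 1 or 2 events need recording only if attributed to trial treatment or if they change or interrupt treatment. Testing, recording and classification can therefore each differ by arm.

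**Step 4: illustration with assumed inputs.** Let n = 240 / 2 = 120 per arm, p = true risk (the same in both arms), and d = proportion of cases detected. Then

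expected observed cases = n × p × d, and apparent risk ratio = d(chloroquine) / d(control).

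Neither p nor d is in the documents; the values below only show the range.

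| p | d chloroquine / control | Expected observed cases | Apparent risk ratio |
|---|---|---|---|
| 3% | 50% / 50% | 1.8 v 1.8 | 1.0 |
| 3% | 50% / 25% | 1.8 v 0.9 | 2.0 |
| 3% | 80% / 20% | 2.9 v 0.7 | 4.0 |
| 5% | 50% / 50% | 3.0 v 3.0 | 1.0 |
| 5% | 50% / 25% | 3.0 v 1.5 | 2.0 |
| 5% | 80% / 20% | 4.8 v 1.2 | 4.0 |
| 10% | 50% / 50% | 6.0 v 6.0 | 1.0 |
| 10% | 50% / 25% | 6.0 v 3.0 | 2.0 |
| 10% | 80% / 20% | 9.6 v 2.4 | 4.0 |

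For example, 120 × 0.05 × 0.50 = 3.0 and 120 × 0.05 × 0.25 = 1.5. The ratio simply returns the assumed detection split. It shows the direction and mechanism of the bias and does not estimate it. The first row for each risk shows the other failure: equal but incomplete detection leaves the ratio at 1.0 and hides half the cases.

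**Step 5: electrolytes.** The stated check follows an event and sits in text about stopping or interrupting chloroquine. No value is scheduled at baseline or in the control arm, although a test done in the 24 hours before entry would be recorded if it happened to exist.

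**The case against.** The strongest reply is that nothing here is misstated. The list of expected toxicities exists to decide whether a serious reaction is unexpected; it does not promise to screen for each item. It names more than thirty, and Table 3 has no dedicated test for several of them, such as corneal deposits or hearing impairment. The protocol adds that the described reactions usually follow high doses or long exposure, and it calls the adverse event comparison informal. With a handful of events per arm, that comparison would be weak in any case. This stands as a reason to treat the point as small. It does not supply an arm-neutral glucose value for a reaction the protocol names repeatedly and could measure on samples already taken.

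A reader might infer that the trial cannot detect hypoglycaemia at all, or finds it only by chance. The documents do not support that: both arms are assessed daily and evaluated for adverse events, so clinically evident cases can surface.

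A reader might also infer that QT prolongation goes unseen because electrolytes are not in the panel. That does not follow. QT prolongation is found by ECG, which the protocol covers separately.

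Lastly, scheduled tests would not remove the discretion in classifying a laboratory abnormality as an adverse event. That is correct, and is why the fix compares the measured values themselves.

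**Conclusion.** The point holds as a limited measurement gap. No glucose is scheduled in either arm, so mild or asymptomatic hypoglycaemia, and hypoglycaemia in unconscious participants, is found through unscheduled tests whose ordering, recording and classification are open to knowledge of the arm. Electrolytes likewise lack a scheduled baseline or comparator value; this is a lesser matter.

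The size of any bias is unknown. The ratios of 2 and 4 are consequences of assumed detection rates and should not be read as predictions. That clinicians would test chloroquine patients more often is a plausible inference from the open-label design; the protocol does not say so. The point also takes footnote a as the complete panel, as it is written. It warrants a cheap improvement and does not call the trial's main conclusion into question.

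**What to change.** Extend Table 3 footnote a to include glucose and the four electrolytes already named under Study intervention, measured in both arms on the chemistry samples drawn at screening and Visits 3, 5 and 7. State that the scheduled post-baseline values will be compared between arms directly, with screening as baseline, alongside the adverse event counts. The comparison then does not depend on who ordered a test or whether the result was called an event.

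The cost is a few extra analytes, with no added visit. The laboratory should confirm that the sample volume is sufficient and whether glucose needs special handling, since the article gives no volume per test. Three post-baseline spot values will miss transient episodes, so they give a like-for-like comparison rather than a full event rate. This is a change to measurement only; no rule for managing patients is proposed.
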